## Abstract

**Aim:**

Young women with psychiatric illness have an increased susceptibility for eating disorders (ED); however, no prevention initiatives have been tested for this group. The Body Project ED prevention program has produced promising effect on ED symptoms, body satisfaction, and future ED onset; however, no studies have investigated this specific vulnerable group. In SMILE Body Project, we adapted the Body Project manual to a psychiatric population. In this protocol paper, we describe the randomized controlled trial (RCT) to evaluate the efficacy of the SMILE Body Project.

**Methods:**

This is an ongoing RCT including 300 young women between 15 and 30 years with a psychiatric illness and subjective body dissatisfaction, starting May 2025. Participants are randomized to either online Body Project groups or an active control arm based on expressive writing exercises. The primary aim is to test if SMILE Body Project significantly reduces the incidence of ED in women with psychiatric illness after 2 years compared to controls. The secondary aim is to explore changes in ED symptoms, psychiatric symptoms, QoL, and predictors such as psychiatric symptoms and time spent on social media.

**Results:**

We expect that SMILE Body Project will effectively reduce the incidence of ED diagnosis compared to controls. In addition, we anticipate new knowledge on how time spent on social media affects body image in women with psychiatric illness.

**Conclusions:**

If SMILE Body Project proves efficacious, it has potential for implementation at low cost and may contribute to broad prevention of future ED onset among young women with psychiatric illness.

**Clinical Trials. gov Identifier:**

NCT06893627

**Supplementary Information:**

The online version contains supplementary material available at 10.1007/s40519-026-01832-w.

## Introduction

Eating disorders (ED) are characterized by body dissatisfaction, dietary restraint, binge eating, and/or compensatory behaviors, such as self-induced vomiting, excessive exercise, and misuse of laxatives and diuretics, with the main diagnostic categories being anorexia nervosa, bulimia nervosa, and binge eating disorder (DSM-5) [1]. EDs are associated with functional impairment, reduced quality of life (QoL), increased co-morbidity, and mortality [2, 3]. Peak incidences for most ED occur between the ages of 16–25 [4] indicating that ED prevention initiatives should be implemented within this specific age group or earlier [5, 6].

Health care costs for EDs, especially anorexia nervosa, are high, few receive diagnosis and treatment, and among those who do, fewer than 50% produce symptom remission [7, 8]. In addition, individuals with binge eating disorders and bulimia nervosa often go untreated for years or even decades [9, 10]. Thus, there is a need for effective evidence-based prevention programs to reduce future onset of ED in the general population, but especially in high-risk groups.

Individuals with other primary disorders such as psychiatric illness and chronic diseases have increased risk of EDs [11, 12]. The risks are fourfold among those with psychiatric illness [12]. For individuals with psychiatric illness, the increased risk might be related to the elevated distress due to psychiatric symptoms or due to interpersonal problems related to the primary disorder or possible shared genetic factors [13]. One of the most dominant risk factors, and primary drivers of EDs, is body dissatisfaction [14]. Body dissatisfaction has been on the rise among adolescents in recent decades [15].

The Body Project is a dissonance-based intervention that helps participants understand how society and social media (SoMe) affect our perception of body and appearances. It is currently the most studied ED prevention program, reducing ED symptoms and future onset of ED by up to 77% (relative risk) over 2 years compared to the control group [16].

The Body Project consists of four 1 h group sessions led by trained facilitators and has primarily been tested in females with body image concerns [17]. The program was developed at Stanford University and the University of Texas at Austin, USA, by [name] [18]. During and between sessions, participants are encouraged to engage in verbal, written, and behavioral exercises in which they collectively critique the thin beauty ideal. These activities lead to a reduction in thin-ideal endorsement by inducing cognitive dissonance, which motivates participants to adjust their beliefs and attitudes to align with the perspectives expressed in the sessions [19]. The reduction in pursuit of the thin ideal results in subsequent decreases in body dissatisfaction, unhealthy dietary restriction, and negative affect, which reduces risk for future ED onset.

Body Project produces significantly greater reductions in thin idealization, body dissatisfaction, dieting, negative affect, and ED symptoms compared to control groups among 15 + year females at post-test and at 2–3-year follow-up [20].

The Body Project is most effective in reducing the onset of new ED when facilitated or co-facilitated by peers. A recent meta-analysis found that the peer-led in-person Body Project intervention reduced the future onset of eating disorders by 58% over a period of 4 years [17]. The Body Project has not reduced future onset of ED when facilitated solely by clinicians [21]. Proposedly, health promotion interventions are perceived as more credible if delivered by individuals who are similar to group participants [22]. Previous studies have mostly been in-person, but recent studies point toward a similar efficacy when delivered virtually [16, 23].

Considering the significant physical and psychological impacts of EDs, it is imperative that research focus on effective and implementable ED prevention. With four online sessions, the Body Project is an easily accessible, scalable, and cost-effective approach to reduce the future incidence of ED and improve overall well-being among vulnerable young women.

## Objectives of the SMILE trial

The present study aims to test the efficacy of the Body Project as a virtually delivered peer-led intervention for women with psychiatric illness and body dissatisfaction.

The primary aim of this study is to reduce the incidence of ED, measured by a clinical diagnostic interview after 2-year follow-up.

Secondary objectives are to examine whether the Body Project intervention leads to (1) reductions in eating disorder symptoms, body dissatisfaction, and thin-ideal internalization, and (2) improvements in QoL, loneliness, and overall psychiatric symptom burden across follow-up assessments.

The Body Project manual has been adapted to include elements relevant for individuals with psychiatric illness, with an increased emphasis on SoMe-related content.

After baseline assessment, participants are randomized to either:

(1) Body Project intervention, or (2) Active expressive writing control condition.

We propose the following hypothesis:I.The Body Project intervention will be effective in reducing incidence of ED (primary outcome) over a 2-year period compared to controls.II.The Body Project intervention will significantly reduce ED symptoms, body dissatisfaction, and thin idealization at all follow-up assessments.III.The Body Project will be effective in reducing total psychiatric symptom load, loneliness and QoL at all follow-ups compared to active controls.IV.Baseline psychiatric symptoms, SoMe use, and body dissatisfaction predict future increases in ED symptoms over a 2-year period.

## Methods

### Research design

A randomized controlled methodology was applied in this study.

### Participants

We aim to recruit 300, 15–30-year-old, women with a psychiatric diagnosis, randomized 1:1 to the Body Project intervention or an active control condition. Participants are allocated using block randomization with varying block sizes and random permutations within each block to ensure allocation concealment and balance across study arms. All participants receive usual care for their psychiatric condition. A participant flowchart is illustrated in Fig. 1.

**Fig. 1 Fig1:**
[figure not shown]
Participant flowchart of the body project SMILE trial

### Recruitment

All participants are self-referrals. Information on the project is available as leaflets, either in print or in SoMe (Instagram and TikTok). A specific research website (www.bodyproject.dk) has been established and contains participant information and contact information. The specific wording in the recruitment “Do you want to beat your body dissatisfaction?” will aid in the natural selection of women at high risk. In addition, a registration form for expression of interest is available. Psychiatric Departments throughout Denmark and educational organizations (upper secondary schools, high schools, vocational educations) in Central Denmark Region and Northern Denmark Region can provide information about the project and hand out the information leaflets. The participant information and information sent to parents to participants < 18 years of age are similar, except for added parental guidance on how best to support their adolescents.

### Inclusion criteria

The following inclusion criteria are utilized: (1) women; (2) 15–30 years; (3) at least one medically verified psychiatric diagnosis diagnosed (e.g., mood disorders, anxiety disorders, ADHD, and personality disorders); and (4) self-reported body dissatisfaction.

Participants may have more than one psychiatric diagnosis, and all psychiatric diagnoses will be recorded at baseline using ICD-10 codes.

### Exclusion criteria

Current ED diagnosis of anorexia nervosa, bulimia nervosa, or binge eating disorder according to DSM-5 criteria or severe subtypes of these corresponding to other specified ED (e.g., clearly self-induced low weight below the 5th percentile for persons below 18 years of age or BMI 17½ in persons 18 + years but without disturbed body perception, vomiting twice a week or more for 3 months but with objective binge being absent or less frequent) as evaluated via the Eating Disorder Diagnostic Interview or history of an ED within the past 12 months. Prodromal cases are included.

Acute psychiatric instability or psychosis or suicide attempt within the last 12 months, or inability to cognitively understand the project or work in the online group setting.

Both inclusion and exclusion criteria are presented in Table 1.

**Table 1 Tab1:** Inclusion and exclusion criteria

Inclusion criteria	Exclusion criteria
Female participants	Current ED diagnosis or clinically significant ED symptoms (DSM-5, via Eating Disorder Diagnostic Interview) or history of an ED within the past 12 months
Aged 15–25 years	Acute psychiatric instability, psychosis, or suicide attempt within past 12 months
Medically verified psychiatric diagnosis (e.g., mood disorders, anxiety, ADHD, and personality disorders)	Cognitive inability to engage in the project
Self-reported body dissatisfaction	Severe substance abuse impairing participation

### The SMILE body project intervention

Minor cultural or disease-specific adaptations to the general Body Project manual have been made, in collaboration with both [name], including participants’ perspectives. The SMILE Body Project will consist of 4 sessions. An overview of content is provided in Table 2. Sessions are held via a secure online platform, uniquely applicable to invited participants. Sessions are recorded as this will enable supervision and fidelity assurance to ensure compliance with the manual. Short individual follow-up contacts via phone will be made if participants miss a session.

**Table 2 Tab2:** Overview of SMILE body project sessions

Session	Content	Home exercises
1	• Discussions, definition and origins of the thin ideal, and costs associated with pursuing the thin ideal	Write a **Letter to a younger girl** struggling with body image concerns including costs associated with pursuing the thin ideal **Mirror exercise,** stand in front of a mirror and look at yourself and write down 10 positive qualities. This includes physical, emotional, intellectual, and social qualities
2	• Present and discuss homework from session 1 • Role plays to elicit verbal statements against the thin ideal	**Talk to two people** and ask them to discuss the main costs of pursuing the thin ideal Generate a **Top-10 list** of things girls/women can do to resist the appearance ideal
3	• Present and discuss homework from session 2 • Role plays and discussions how to resist the thin ideal, how to challenge personal body-related concerns, and how to respond to future pressures to be thin • Discussion on the influence of social media on body image perception	As a **Behavioral Challenge**, do two things that you currently do not do because of body image concerns to increase your confidence Please choose two behaviors from your Top-10 list to do between sessions as a **Body Activism** exercise Choose at least one way to challenge appearance ideals and promote a healthier approach to **social media** Write a letter or create a list of advice to your y**ounger self**, using what you’ve learned in the group to show how to prevent body image concerns and build a positive self-image
4	• Present and discuss homework from session 3 • Discuss how the ways in which we talk about our bodies may promote the thin ideal • Have participants come up with more positive alternative ways of talking about their bodies and encouraging participants to continue to challenge their body image issues in the future	As a **self-affirmation** exercise, choose three ideas to keep challenging your body image concerns and work toward developing a positive body image

Each group will consist of 6–8 group members as in previous studies [16, 23, 24]. The groups are led by two peers. The peers are trained young adults, preferably with personal experience of psychiatric illness, i.e., students within the area of health care (medicine, dietetics, psychology, and nursing).

All peers have received extensive and continuous training and supervision. The training will be made available as online sessions based on the manuscript and in collaboration with [name]. Fidelity assurance and continuous monitoring and evaluation of sessions will be performed during bimonthly supervision. Previous fidelity testing has shown high inter-rater agreement for the original Body Project [25].

### Active control condition

The expressive writing (EW) serves as the active control condition and will consist of written instructions sent to participants weekly via text message over 4 weeks, asking them to write about their thoughts, emotions, images, and other content related to their body. They are encouraged to sit undisturbed for 40 min (no more, no less) and write only to themselves. If, after a while, they do not know what to write, they are encouraged to repeat what they have already written. This version of EW was used as earlier trials have found them equally credible to the Body Project [16].

The output is solely for the participants themselves and will not be read by others.

## Measures

Applying measurements from existing Body Project literature will allow for comparison to effects reported in previous trials, which will facilitate interpretation of our findings. All questionnaires will be set up in REDCap. Questionnaires have been translated and back-translated according to guidelines [27].

### Primary outcome measures

*ED diagnosis*: The semi-structured Eating Disorder Diagnostic Interview (EDDI) assesses ED symptoms, including binge eating and purging, and will be used to determine anorexia nervosa, bulimia nervosa, binge eating disorder, and purging disorder [28]. The interview will be performed by video/telephone by an experienced clinician/researcher.

### Secondary outcome measures

ED risk factors and symptoms:*Thin idealization*: Ideal-Body Stereotype Scale–Revised to assess pursuit of the thin ideal [29].*Body dissatisfaction*: Body Dissatisfaction Scale to assess dissatisfaction with various body parts [21, 30].*Overevaluation of appearance, weight and shape* will be measured by selected items from the Eating Disorder Examination Questionnaire Eating behavior (EDE-Q) items 22, 23*Dieting*: Dutch Restraint Eating Scale (DRES) to assess frequency of dieting behaviors [31].*Binge eating*: will be measured by EDE-Q items 13, 14, 15 [32]

Mental health:*Anxiety symptoms*: Anxiety experienced within the past 14 days was measured using the Generalized Anxiety Disorder 2-item scale (GAD-2) [33].*Functional Impairment*: will be examined using the Clinical Impairment Assessment (CIA), to examine psychosocial impairment due to ED symptoms [34].*Depression symptoms*: Depression experienced within the past 14 days will be measured using the Patient Health Questionnaire 2-item scale (PHQ-2) [35].*Positive and Negative affect* will be assessed using *PANAS SF* [36].*Stress* will be assessed using the single item: “How often do you feel stressed?” [37].*Psychological distress* will be assessed using Brief Symptoms Inventory 18 (BSI-18) [38].Social Behavior will be assessed using *Social Adjustment Scale* [39].*Loneliness* will be assessed through BSI item 5.

Other*Demographic characteristics* will be collected, including familial and living status, work/educational status, somatic or psychiatric illness and related treatment, weight and height, physical activity, sleep problems, substance use, and eating disorders in family.*Health Care Utilization* during the past 1 month will be assessed using two items: (1) the number of times participants saw specific health care professionals because of physical or psychological illness, respectively, and (2) the number of times the participant saw a psychologist, psychiatrist, counselor, or therapist due to mental health problems.*Social media use* will be assessed using multiple items to generate two distinct measures: one capturing time spent on various platforms, and another evaluating the perceived influence of social media on body satisfaction and self-perception [40].

### Power calculations

The incidence of new onset of ED over a period of 2 years is determined via the EDDI at baseline and 1- and 2-year follow-up. Based on the incidence of ED in the study by Ghaderi and colleagues, we expect significant differences between groups, with an incidence of ED in the control group of 8.8% and 2% in the intervention group [16]. We accept a significance level of 0.05 (*α*) and a power of 0.80 (*β*), leading to a sample size of 137 in each arm. To accommodate for potential attrition, we aim to include 150 in each arm. Attrition rates have been reported as increasing by 12% at 2 years and 19% at 4-year follow-up [21].

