### Statistical analysis

Analyses will follow the intention-to-treat (ITT) principle, with participants analyzed in their randomized groups. The primary outcome, onset of a clinical ED by 2-year follow-up, will be analyzed using logistic regression with study condition as the independent variable. Results will be reported as odds ratios (ORs) with 95% confidence intervals (CIs). Secondary outcomes, including continuous measures of ED symptoms, body dissatisfaction, psychiatric symptom load, and QoL across five timepoints (baseline, post-intervention, 6 months, 1 year, and 2 years), will be analyzed using linear mixed-effects models (LMMs). These models will include fixed effects for study condition, time, and their interaction, with random intercepts for participants and groups to account for within-subject correlation and clustering of participants within groups. Where appropriate, random slopes for time will be explored. Effect estimates will be reported with 95% CIs.

Baseline characteristics will be summarized using descriptive statistics. Between-group comparisons will use *t* tests or Mann–Whitney *U* tests for continuous variables (depending on distribution) and *χ*^2^ or Fisher’s exact tests for categorical variables. Effect modification will be examined by testing interactions between intervention assignment and baseline psychiatric diagnosis, as well as between intervention assignment and diagnostic complexity (single versus multiple psychiatric diagnoses), via interaction terms in the regression models. Missing data will be handled using multiple imputations. All statistical tests will be two-tailed with *α* = 0.05.

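### The 137 per arm gives about 70% power under the stated two-tailed 5% test, not 80%, and fits a one-tailed calculation

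*Protocol article*

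**What the plan says.** The Power calculations section takes its rates from an earlier trial of the programme, "with an incidence of ED in the control group of 8.8% and 2% in the intervention group", sets alpha at 0.05 and power at 0.80, and reports the result as "leading to a sample size of 137 in each arm". It does not say whether the calculation was one- or two-sided and names no formula. It then adds a margin: "To accommodate for potential attrition, we aim to include 150 in each arm". The same paragraph cites 12% attrition at 2 years.

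The Statistical analysis section fixes the test. Onset of a clinical eating disorder by 2 years "will be analyzed using logistic regression with study condition as the independent variable", and "All statistical tests will be two-tailed" at the 5% level. The Participants section gives the allocation: "randomized 1:1 to the Body Project intervention or an active control condition".

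**The concern.** A sample size is tied to the test it was computed for. With 8.8% against 2%, a two-sided 5% test and 80% power, 137 per arm looks too small. It is about the size that the same inputs give one-sided. If so, the trial has less power for its primary hypothesis than it reports. A reader who takes the 80% at face value would give a null result more weight against the programme than the design supports. The assumed effect is already large: 2/8.8 = 0.227, a 77% relative reduction. Any smaller true effect lowers the power further.

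**Working it through.** **Inputs.** From Power calculations: p1 = 0.088, p2 = 0.02, alpha = 0.05, power = 0.80, stated n = 137 per arm, planned enrolment 150 per arm, 12% loss at 2 years. From Statistical analysis: two-tailed, logistic regression. From Participants: 1:1 allocation.

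**Quantities used throughout**
- Difference d = 0.088 − 0.02 = 0.068; d² = 0.004624
- Mean rate = (0.088 + 0.02)/2 = 0.054
- A = √(2 × 0.054 × 0.946) = 0.3196
- B = √(0.088 × 0.912 + 0.02 × 0.98) = 0.3160
- z for power 0.80 = 0.8416; z for 5% one-sided = 1.645; z for 5% two-sided = 1.960

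**Step 1: reproduce 137**
- Standard formula, one-sided: n = (1.645A + 0.8416B)²/d² = 135.6, so 136.
- Simple pooled formula, one-sided: n = (1.645 + 0.8416)²A²/d² = 136.6, so 137, the stated figure.
- One-sided power at 137, standard formula: 80.4%.

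**Step 2: apply the two-tailed rule**
- Standard formula: n = (1.960A + 0.8416B)²/d² = 172.2, so 173.

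| Two-sided method | n per arm for 80% |
|---|---|
| Arcsine | 155 |
| Unpooled | 170 |
| Standard | 173 |
| Simple pooled | 174 |
| Standard with continuity correction | 201 |
| Log odds ratio, Wald | 207 |

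The smallest is 18 above 137.

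**Step 3: two-sided power at the planned sizes**

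Normal approximation: power = Φ((d√n − 1.960A)/B).
- n = 137: Φ(0.536) = 70.4%
- n = 132 (150 × 0.88): Φ(0.490) = 68.8%
- n = 150 (no loss): Φ(0.653) = 74.3%

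At 137 per arm the expected counts are only 137 × 0.088 = 12.1 and 137 × 0.02 = 2.7 events, so power was also obtained by summing exact binomial probabilities over all outcomes that each two-sided test rejects:

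| Test | 132 per arm | 137 per arm | 150 per arm |
|---|---|---|---|
| Fisher | 60.4% | 62.7% | 68.2% |
| Wald (log odds ratio) | 61.4% | 64.2% | 68.7% |
| Pearson chi-square | 71.8% | 73.6% | 77.6% |
| Likelihood ratio | 75.0% | 76.5% | 80.0% |

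At 137 per arm the type II error is therefore 23.5% (likelihood ratio) to 37.3% (Fisher), against the claimed 20%.

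**Step 4: what 80% would take.** On the standard formula, 173 evaluable per arm, or 346 in total. Allowing for 12% loss, 173/0.88 = 196.6, so 197 per arm.

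**The case against.** Four points can be made for the plan.

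- **The one-tailed origin is inferred.** This stands: the article names no sidedness and no formula. A two-sided log-rank calculation that treats the risk ratio 0.227 as a hazard ratio needs 15 events, and 15/0.108 = 138.9, so 139 per arm, which is close to 137. But no time-to-event analysis is planned, and the hazard ratio implied by the two incidences, ln(0.98)/ln(0.912) = 0.219, gives 14 events and 130 per arm. Wherever 137 came from, it falls short under the stated two-tailed test.
- **The 2% may be rounded.** A two-sided arcsine calculation falls to about 139 at 1.75%. However, the Introduction gives a reduction of up to 77% from the same source, and 8.8% × 0.23 = 2.02%, so the true input was probably very near 2%.
- **Power depends on the test, and 70% is an approximation.** This also stands. The likelihood-ratio test, a natural choice for logistic regression, does best: 76.5% at 137, and 80.0% at 150 if nobody is lost. After 12% loss it is 75.0%. The Wald test, equally natural for that model, gives 64.2% at 137, and still only 77.3% at 173.
- **Type I error is untouched and confidence intervals will be reported.** True. The defect lies in the power claim, not in the validity of the test, and the intervals will show the imprecision to a careful reader.

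**Conclusion.** The concern holds. At 8.8% against 2% with a two-tailed 5% test, 137 evaluable per arm gives about 70% power on the standard approximation and 63% to 76% by exact calculation. None of these reaches 80%. After the cited 12% loss from 150, the corresponding figures are about 69% and 60% to 75%. The stated size is what a one-sided two-proportion formula gives, which is the probable but undocumented explanation.

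The result rests on the two rates as printed, 1:1 allocation, independent participants, and an unadjusted comparison of the arms. Since the stated power for the primary outcome is wrong as written, it must be corrected.

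**What to change.** Rewrite the Power calculations paragraph to say that:

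- the calculation is two-sided at 5%, for 8.8% against 2%;
- power is about 70% with 137 evaluable per arm, about 69% with 132 (150 less 12%), and about 74% with 150;
- 80% power would need about 173 evaluable per arm on the two-proportion formula;
- a named test was used, and it is the one that will be applied in the logistic regression.

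The figures in the second and third items belong to the two-proportion z-test. If the primary test is to be the Wald or likelihood-ratio test from the logistic model, give the figures for that test instead: at 132, 137 and 150 per arm, 61%, 64% and 69% for Wald, or 75%, 76% and 80% for likelihood ratio. The 173 would then also be replaced by the number for that test; for Wald, the log odds ratio formula gives 207.

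The cost is the wording of one paragraph and a less favourable stated power. Enrolment, design and analysis need not change for this correction.

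### The planned 150 per arm does not absorb the 12% two-year attrition cited beside it: about 132 per arm would have a 2-year interview, against the 137 required

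*Protocol article*

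**What the plan says.** All the figures stand in one paragraph of the protocol article, Power calculations. The assumed two-year incidences are given as "with an incidence of ED in the control group of 8.8% and 2% in the intervention group". The requirement follows: "We accept a significance level of 0.05 (*α*) and a power of 0.80 (*β*), leading to a sample size of 137 in each arm". The paragraph then adds "To accommodate for potential attrition, we aim to include 150 in each arm", and closes with "Attrition rates have been reported as increasing by 12% at 2 years and 19% at 4-year follow-up".

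Two other sections bear on the point. Participants gives the allocation: "randomized 1:1 to the Body Project intervention or an active control condition". Statistical analysis sets the primary time point ("The primary outcome, onset of a clinical ED by 2-year follow-up, will be analyzed using logistic regression") and the sidedness ("All statistical tests will be two-tailed with *α* = 0.05"). It also specifies analysis by intention to treat, with multiple imputation for missing data. The power paragraph does not say whether its own calculation is one-sided or two-sided.

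**The concern.** The paragraph presents 150 as the number that makes room for attrition. Beside it stands a loss rate, at the primary time point, that 150 does not make room for. No lower rate is offered to explain the choice of 150. A reader will take it that the 80% power attached to 137 survives the expected loss, but on the paragraph's own figures the number with a 2-year interview falls below 137. At stake is the accuracy of the power statement. The design itself is not in question here.

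**Working it through.** **Inputs.** From Power calculations: p1 = 0.088 (control), p2 = 0.02 (intervention), α = 0.05, power 0.80, 137 required per arm, 150 planned per arm, 12% attrition at 2 years. From Participants: 1:1 allocation. From Statistical analysis: two-tailed tests.

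**Step 1: reproduce 137.** The article gives no formula. The usual pooled normal approximation is

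n = [z_α·√(2p̄(1−p̄)) + z_β·√(p1(1−p1) + p2(1−p2))]² / (p1−p2)²

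with p̄ = (0.088 + 0.02)/2 = 0.054, so that:

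- √(2 × 0.054 × 0.946) = 0.3196
- √(0.080256 + 0.0196) = 0.3160
- (p1−p2)² = 0.068² = 0.004624

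Results:

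- One-sided: (1.645 × 0.3196 + 0.842 × 0.3160)² / 0.004624 = 135.6, so 136 per arm.
- Two-sided: (1.960 × 0.3196 + 0.842 × 0.3160)² / 0.004624 = 172.2, so 173 per arm.

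The one-sided version is the closest match to 137, one participant away. The two-sided version does not match. Other two-sided formulas do not match either: 170 unpooled, about 155 arcsine, 201 with continuity correction, about 207 on the log odds ratio. That 137 came from a one-sided calculation is therefore an inference.

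**Step 2: the attrition allowance.**

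- Largest loss that 150 can absorb while keeping 137: 1 − 137/150 = 8.7%.
- Number left at 12% loss: 150 × (1 − 0.12) = 132 per arm, which is 137 − 132 = 5 short.
- Number needed to keep 137 at 12% loss: 137/0.88 = 155.7, so 156 per arm.
- Cruder shortcut: 137 × 1.12 = 153.4, so 154 per arm.

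Both conventions give more than 150, so neither the choice of formula nor rounding explains the gap.

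**Step 3: what the gap costs in power.** With the same approximation,

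power = Φ{[0.068·√n − z_α × 0.3196] / 0.3160}

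| Per arm | One-sided 5% | Two-sided 5% |
|---|---|---|
| 150 (no loss) | 83.4% | 74.3% |
| 137 | 80.4% | 70.4% |
| 132 | 79.1% | 68.8% |

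For example, two-sided at 132: (0.068 × 11.489 − 1.960 × 0.3196)/0.3160 = 0.490, and Φ(0.490) = 0.688.

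Going from 137 to 132 costs 80.4 − 79.1 = 1.3 points one-sided and 70.4 − 68.8 = 1.6 points two-sided.

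**The case against.** **The sentence states a purpose, not a guarantee.** It says why 150 was chosen and does not claim that 150 covers 12%. The 12% is a rate reported in a cited study and is not labelled as this trial's planning assumption. This stands in part. A reader might infer that the attrition sentence is flatly false, and the wording does not support that. What it supports is narrower: the allowance is smaller than the only two-year rate cited, and no other rate is given. The wording of the 12% is loose, but 12% lost by two years is the natural reading.

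**Intention to treat and multiple imputation keep everyone in the analysis.** They keep the denominator, but they do not recreate the information in interviews that never took place. The protocol itself treats attrition as a cost in sample size, since it goes above 137 for that reason.

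**The 1-year interview recovers information.** This stands in part. The outcome is onset by two years, and the diagnostic interview is also held at one year. A participant diagnosed at one year and lost afterwards already has a known outcome, and others seen at one year contribute to the imputation. So 132 is a conservative count of the information available. A 1-year interview cannot show onset, or its absence, in the second year, and the documents do not allow the recovered amount to be calculated.

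**The effect is trivial beside the uncertainty in the borrowed incidences.** The effect is indeed small. It remains a discrepancy within one paragraph that can be corrected in a sentence.

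**Conclusion.** The point holds as a small inconsistency. The plan allows for at most 8.7% loss and cites 12% at the primary time point. At 12%, about 132 per arm have a 2-year interview, 5 per arm below the stated requirement, and power falls by 1 to 2 points. This rests on the incidences of 8.8% and 2%, on 12% meaning the share lost by two years, on the pooled normal approximation, and on giving no credit for the 1-year interviews.

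Two stronger readings are not supported:

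- A reader might put the whole distance from 80% to about 69% down to attrition. Most of it is not. At 137 evaluable, with no shortfall, two-sided power is already 70.4%. That difference comes from the sidedness of the base figure, which is a separate matter; attrition adds only the last 1.6 points.
- A reader might conclude that keeping loss to 8.7% would secure 80% power. That takes 137 as a sound base. Under the two-tailed test prescribed in Statistical analysis, the pooled requirement is 173 per arm, so 150 falls short even with no loss (74.3%).

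**What to change.** In Power calculations, state that 150 per arm gives about 132 evaluable per arm at 12% attrition. Quote the power at 132 under the two-tailed test, about 69% for 8.8% versus 2%, in place of the implied 80%, and name the test and the approximation used. A clause may note that 1-year interviews could recover part of the loss.

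This is a change of wording only, with no change to recruitment, follow-up or analysis. The cost is that the stated power becomes less favourable. Raising the target to 156 would close the attrition gap but would not restore 80% two-tailed power: with 137 evaluable it would be 70.4%.
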